**Detailed research project :****I. Problem, hypothesis and objectives of the investigations**

## **I.1 . Peripheral lung nodules**

Peripheral lung nodules are an increasing motive of consultation in respiratory medicine (1, 2). This is partly due to the increasing part of peripheral lung adenocarcinoma among primary lung cancers in developed countries (3), and partly to the increasing use of Chest CT scan in asymptomatic high risk subjects.

Chest CT has been used for early lung cancer detection programs in both North America and Japan for more than a decade. (4). These programs have showed a very high frequency of peripheral lung nodules in North America population, since nearly 20 % of the explored subjects have one or several small nodules on baseline screening CT. In USA, 50 % of 50 years old smokers may have an infracentimetric nodule on chest CT (5). From these lesions, identification of malignant nodules is important because they represent a potential curable form of cancer. Whereas the prevalence of malignancy may vary among studies, the vast majority of the lesions smaller than 8 mm are benign, mostly granulomas and hamartoma. In screening studies, the prevalence of malignancy ranges between 2 to 13% of the patients with nodules. In contrast, PET CT studies of lesions larger than 2 cm have shown a prevalence of 48 to 82% of cancers (1). This underlines the need for a rigorous diagnostic strategy of peripheral lung nodules, according to the size of the lesion and the estimated subject's risk for lung cancer (4).

Until recently there was no scientific validation of CT screening of lung cancer (6, 7). However, the recent release of American NCI sponsored NSLT trial results (8), may impact the clinical practice in a near future. Early results of this randomized trial indicate "twenty percent fewer lung cancer deaths seen among those who were screened with low-dose spiral CT than with chest X-ray". If confirmed, these data will imply that in industrialized countries, the number of asymptomatic subjects undergoing a chest CT scan will increase significantly, so will do the number of patients presenting with a peripheral lung nodule in daily practice

Both Fleischner Society and ACCP have provided guidelines for the management of pulmonary nodules (1, 9), which give a large place for repeated follow-up CT imaging procedures and PET-CT, before taking the decision of histology sampling. In North America, compliance to these guidelines appears acceptable (10). PET-CT false negatives are well known, including resolution limits of the nuclear imaging devices or a low metabolic activity in some cancer lesions such as bronchiolo-alveolar carcinomas and carcinoid tumors. Besides chronic lung bacterial infections (*Nocardia*), mycobacterial diseases, aspergillosis, sarcoidosis and pulmonary vasculitis are well known causes of false positive PET-CT results. Because positive and negative predictive value of PET – CT is only 75%, it is generally admitted that a positive PET CT needs histology sampling to be performed, whereas a negative PET –CT requires imaging follow up for two years. (11). However, due to high probability of lung cancer, non calcified nodules larger than two cm are usually biopsied.

## **I. 2. Endoscopic diagnosis and sampling of peripheral pulmonary nodules.**

The histology of a peripheral nodule larger than 1cm can generally be obtained before surgical resection, either by CT guided transthoracic biopsy (TTB) or endoscopically. Recent endoscopic techniques, referred as

navigational bronchoscopy, have the ability to localize and sample peripheral lung nodules larger than 1 cm in size (12). Studies have demonstrated that these techniques have a rentability that is equivalent to transthoracic biopsy sampling but a smaller risk of pneumothorax. (12). The endoscopic procedure for peripheral lung nodule exploration is preferable to TTB in patients suffering from severe respiratory insufficiency, where a iatrogenic pneumothorax may be life threatening, or if the nodule is situated in a central position or at more than 1 cm from the pleura.

Navigational bronchoscopy takes advantage of computing advances in CT image reconstruction, such as virtual bronchoscopy (2). In this case, bronchoscopy is preceded by reconstruction of segmental and subsegmental inner bronchial surface, computed from the high resolution CT scan. Using this technique, the precise bronchial and segmental pathway (or road map) to the tumor can be forecasted before the endoscopic procedure. Two recent techniques, endobronchial ultrasound using high frequency radial probe (EBUS), and electromagnetic navigation (EMN) have been developed in order to localize peripheral nodules and masses during bronchoscopy. Both devices can be associated with virtual bronchoscopy (12), and make use of the extended working channel (EWC) or guide sheeth technique. EWC is a catheter that surrounds the locatable guide of EMN or EBUS miniprobe and can be extended with it through the bronchoscope working channel down to the lesion to sample. Once the peripheral lesion localized, the probe can be removed, leaving the EWC close to the tumor, through which can be introduced a biopsy forceps or a cytology brush. (13, 14).

Localisation of the nodule is not always easy, depending on the presence of a bronchial sign on CT. Characteristic images can be obtained in real time using EBUS when the nodule is reached (figure 1) . EMN makes use of a steerable probe containing an electromagnetic sensor. A specific board inserted on the back of the patient's thorax, produces an electromagnetic field. In this technique, sensor location can be determined in real time within this field , based on Chest CT data and coordonates of known anatomic structures such as main carinas of large bronchi. (figure 2). This technique makes it possible to progress down to the nodule / target with a precision of 2-3 mm. (15, 16).

A randomized trial comparing both EBUS / EMN and their association has shown that each technique has a sensitivity of 65 % for the localisation and diagnosis of peripheral lung nodule, independently from their size (smaller or larger than 2cm) . These techniques do not appear to be strictly equivalent as EBUS provides better results for the nodules located in the lower lobes, that are more mobile, and EMN better results in the upper lobes. In this trial the association of both technique did improve the performance of the navigational endoscopy (80% succes). Owing to the related costs of the technique, an strategy could be to make use of EMN for the upper lobe lesions while using EBUS for the lower lobes.

[figure not shown]

**Figure 1 : EBUS imaging of a 1 cm peripheral lung cancer.** (Pr [name], Rouen University Hospital)

[figure not shown]

**Figure 2: Electromagnetic navigation.**

Real time visualisation of the sensor probe progression to the tumor visualized on axial, sagittal and coronal CT scan reconstructions. Lower right panel , real time control of the distance from the center of the target. (Pr [name], CHU de Saint Etienne)

A noticeable advantage of navigational bronchoscopy is the possibility to place fiducial gold markers within or close to the tumor during bronchoscopy. These radio-opaque markers are highly useful combined with robotized stereotactic radiation therapy techniques such as with Cyberknife, which may be the only available treatment of peripheral lung cancer in patient with advanced respiratory insufficiency.

The main current limitations of navigational bronchoscopy is that the technique cannot differentiate malignant from benign tumors in real time and the low precision for the localisation of the lesion, which is only centimetric.

In this trial we propose to assess a new optical device, called probe based confocal laser endomicroscopy, for the diagnosis of peripheral lung nodule, in comparison with EBUS or EMN.

### **3. In-vivo imaging of peripheral lung diseases and nodules using probe based confocal laser endomicroscopy.**

Probe based confocal laser endomicroscopy (pCLE) of the distal lung is a new optical technology based on the principle of confocal microscopy where the objective has been replaced by a thin (1mm) fiber-bundle or miniprobe.

For in-vivo imaging, the confocal miniprobe is introduced through the working channel of the endoscope and gently advanced down to the tissue to obtain microscopic imaging of the fluorescent structures, in response to 488nm blue light tissue excitation. pCLE makes it possible to visualize microscopic structures 3  $\mu\text{m}$  in size in real time, for a field of view of 600  $\mu\text{m}$  and depth imaging of 50 $\mu\text{m}$ . pCLE is currently commercially provided by Mauna Kea Technologies (Paris, France), as a medical device called Cell-Vizio.

Specific optical miniprobes devoted to the exploration of the lung have been first developed at the Rouen University hospital in 2006, where the technique of distal lung imaging has been set up and the first confocal endomicroscopic images of both proximal bronchi and alveoli could be obtained (17, 18). We have shown that Cellvizio makes it possible to prolonge the endoscopic vision to the most distal parts of the lungs, i.e. terminal and respiratory bronchioles as well as alveolar ducts and sacs. (19).

Since 2006, in vivo confocal imaging of the distal lung (a procedure also called Alveoscopy) has been used at the Rouen University – Pulmonology Clinic, in nearly 200 patients as part of a prospective clinical trial (Alveole trial, ClinicalTrial.gov identifier: NCT00213603).

During this trial, we have shown that the technique makes it possible to image both the elastin network of the bronchial wall in vivo (20), and the interstitial elastic fibered network of the distal lung. (19). We have described the optical appearance of normal alveolar ducts and sacs in-vivo in both non smoking subjects and active smokers (figure 3) and showed the perfect tolerance of the technique in awake, spontaneously breathing patients and healthy volunteers. In smokers, Alveoscopy makes it possible to image the cellular alveolar infiltration

from activated fluorescent macrophages. (figure 3) (19). This minimally invasive technique produces very specific images in real time in diffuse interstitial lung diseases such as lung alveolar proteinosis (21).

In a preliminary study (22) we have shown significant differences in the elastic network organisation of the distal lung between healthy controls and patients suffering from lung fibrosis, asbestosis and silicosis, as well as sarcoidosis.

[figure not shown]

In vivo alveoscopy, non smoker

In-vivo alveoscopy, heavy smoker

**Figure 3. In vivo alveoscopy of healthy controls** (CHU de Rouen, protocole Alvéole).

Left panel, normal elastic network imaging in a non smoking subject, right panel : macrophage alveolar infiltration in a smoker. .

Recent data from our group indicates that Alveoscopy *has the potential to provide in-vivo microscopic imaging of peripheral lung nodules and cancers in real time.* (23). This is made possible without exogeneous fluorophore, because of the alterations of the fluorescent elastic network in the tumor tissue. The visualisation of the tumoral cells is also possible after in situ disposition of non-toxic cellular fluorophores such as methylene blue and 660 nm excitation. Figure 4. (23-26).

Before being implemented into clinical practice, our results must be first confirmed from an independant series of patients. In this multicentric trial, we propose to evaluate Alveoscopy, for the diagnosis of peripheral lung nodules, in vivo, in real time. For this purpose, we aim to compare Alveoscopy results with those obtained in the same patients using navigational bronchoscopy techniques.

[figure not shown]

**Figure 4 . In vivo confocal imaging of a normal alveoli and a peripheral lung adenocarcinoma (Cellvizio).**

A. Normal alveolar duct 488 nm excitation. B. desorganisation of the distal elastic network inside the nodule 488 nm excitation C. In vivo confocal cellular imaging of the nodule after in situ instillation of methylen blue 660 nm excitation. (from [name] et al. (23))

**Our hypotheses are :**

(a), pCLE has the same sentivity than modern navigational endoscopic techniques such as EBUS or EMN for the diagnosis of peripheral lung nodules.

(b) pCLE is able to differentiate in vivo in real time malignant nodules from benign lesions.

The objectives of this study are to assess the ability of pCLE for the precise localization of peripheral lung nodules, and to compare this ability with performances of EBUS or EMN navigation techniques. In this trial, pCLE imaging will considered as successful, if a « solid microscopic patern » can be obtained in vivo, and a diagnosis obtained from the biopsy. These datas will be compared to those of navigation bronchoscopy in the same subject. Positivity criteria for navigational bronchoscopy will be : positive (or contributive) biopsy AND characteristic image using EBUS or progression of the EMN steering probe to less than 5mm of the tumor.

## **II. Méthods**

### **II. 1. General organisation of the research project.**

Prospective, multicentric, open-labeled study, assessing a new optical technology for the diagnosis of peripheral lung nodules, in vivo, in real time.

#### *II.1.1 Patients and procedures:*

Patients with peripheral lung nodule requiring biopsy sampling by navigational bronchoscopy (EBUS or EMN) will be recruited in three French centers : (Pr [name] - CHU de Rouen, Pr [name] - CHU de Saint Etienne, [name] - CHU de Toulouse). These three centers are currently equipped with EBUS , Electromagnetic navigation and probe based confocal microendoscopy (Cell Vizio)

During the procedure, at least one normal alveolar area will be imaged using pCLE on the same side than the peripheral lung nodule to serve as normal control. After a successful tentative of nodule localisation using navigational bronchoscopy, the cellvizio miniprobe will be introduced into the extended working channel for confocal in situ imaging. If confocal imaging fails to show a solid network pattern, a biopsy will be performed and the investigator will be authorized to move the navigational device ( EBUS or EMN) to another position, followed by another confocal imaging and biopsy. A maximum of three attempts to obtain a solid pattern using confocal will be authorized in each patient, after what the procedure will be considered as « failed ». When a solid confocal pattern is obtained, an IV injection of 5 ml fluoresceine sodium 1% will be performed for another imaging before biopsy sampling.

In each case, confocal images will be annotated with the precise identification of the biopsy performed, the images will be stored and a digital copy sent to the Rouen University Hospital for further analysis.

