**Objective(s) of the clinical study**

1. To demonstrate that confocal endomicroscopy is not inferior to navigational endoscopy for the localisation of peripheral lung nodule
2. To demonstrate that confocal endoscopy can differentiate benign from malignant tumors

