**Experimental plan:**

Multicentric prospective controlled trial, conducted in three academic centers, specialized in interventional bronchoscopy, equipped with both navigational bronchoscopy and probe based confocal microendoscopy techniques.

120 subjects with peripheral lung nodule requiring navigational bronchoscopy will be included in the study and explored using both Confocal endoscopy AND navigational bronchoscopy. Confocal probe will be inserted in the same catheter as used for the navigational bronchoscopy and confocal images will be recorded before and after fluorescein IV injection, and before sampling.

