### **III. Research trial**

#### **III. 1. Hypotheses**

(a), pCLE has the same sensitivity than modern navigational endoscopic techniques such as EBUS or EMN for the diagnosis of peripheral lung nodules.

(b) pCLE is able to differentiate in vivo in real time malignant nodules from benign lesions.

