#### **III.2. Objectives**

##### *III.2.1. Primary objective*

To determine if Alveoscopy can help to the localization and sampling of a peripheral lung nodule in vivo in showing a solid pattern.

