### **IV. 4. Endoscopy procedure**

- Alveoscopy procedure will be performed according to the procedure validated at the Rouen University Hospital, in gently advancing the confocal miniprobe through the bronchoscope working channel and distal bronchus until the alveolar fluorescent signal could be obtained. The probe will then stay in place

5 to 30 seconds for alveolar sequence recording

- Navigational bronchoscopy (EBUS / EMN) will be performed according to the usual validated procedure.
- Confocal imaging of the peripheral nodule will be performed by entering the confocal miniprobe into the extended working channel during the navigational bronchoscopy procedure as described in chapter II.1.1..
- Confocal exploration duration will not exceed 10 minutes for the totality of the endoscopy procedure.
- Usual monitoring (EKG, transcutaneous arterial saturation) will be recorded continuously during the procedure, and chest radiograph performed after the bronchoscopy to control the absence of pneumothorax.
- Patient could be discharged after the procedure after one hour, and physical examination.

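### The design can show how often confocal imaging confirms a position that navigation has reached, but not that it is non-inferior to navigation for localising nodules

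*Protocol*

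**What the plan says.** **Claim.** Objective 1, in the opening summary and again in the Synopsis, reads "To demonstrate that confocal endomicroscopy is not inferior to navigational endoscopy for the localisation of peripheral lung nodule". Hypothesis (a), in section I and in III.1, is that "pCLE has the same sensitivity than modern navigational endoscopic techniques". Both treat the two techniques as rival means of finding the nodule.

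**Procedure.** Section II.1.1 fixes the order: "After a successful tentative of nodule localisation using navigational bronchoscopy, the cellvizio miniprobe will be introduced into the extended working channel". Section IV.4 gives the same route, with the nodule imaged "by entering the confocal miniprobe into the extended working channel during the navigational bronchoscopy procedure". If no solid pattern is seen, a biopsy is taken and "the investigator will be authorized to move the navigational device ( EBUS or EMN) to another position, followed by another confocal imaging and biopsy". The limit is stated as "A maximum of three attempts to obtain a solid pattern using confocal will be authorized in each patient".

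**Scoring.** Section III.3.1 scores navigation positive on a conclusive biopsy at the first attempt. It scores pCLE positive on a solid pattern plus a conclusive biopsy at any of the navigational attempts. The validity criterion is recognition of at least 90% of the nodules that navigation localised and sampled.

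**Two further statements bear on this.** Section III.2.1 words the primary objective as an adjunct role: "To determine if Alveoscopy can help to the localization and sampling of a peripheral lung nodule in vivo in showing a solid pattern". The Synopsis (Experimental plan) says that 120 subjects "will be included in the study and explored using both Confocal endoscopy AND navigational bronchoscopy", without making confocal imaging of the nodule conditional on successful navigation.

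**The concern.** A non-inferiority claim about localisation needs each technique to have its own chance of finding or missing the nodule. Here pCLE is given the nodule's position by the comparator, looks through the comparator's catheter, and is judged on the comparator's successes. No section describes pCLE searching for a nodule on its own or after navigation has failed.

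At stake is the headline conclusion. If the 90% criterion is met, the objective as worded invites the statement that pCLE localises nodules as well as navigation does, and the data could not bear that out. The protocol also says that the results might show superiority of confocal imaging, and that would be open to the same misreading.

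**Working it through.** This is mainly a matter of design logic; the arithmetic shows which tables the protocol's own figures imply.

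**1. The protocol's sample size.** Inputs from III.3.2: 78 navigation-positive patients and a forecast navigation sensitivity of 65%. 78 / 0.65 = 120, as stated. The criterion thus rests on 78 patients selected because navigation succeeded.

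**2. What one placement can show.** Navigation-positive requires a conclusive biopsy. pCLE-positive requires a conclusive biopsy and a solid pattern. At the first placement, pCLE-positive patients are therefore a subset of navigation-positive patients. The quantity estimated is positive agreement: (pCLE-positive and navigation-positive) / (navigation-positive). It says nothing about nodules that navigation did not reach.

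**3. What several placements can show.** Take a patient whose first biopsy is inconclusive and whose first image shows no solid pattern. If the navigation device is moved and the second position gives a solid pattern and a conclusive biopsy, III.3.1 scores the patient navigation-negative and pCLE-positive. Pairs positive on pCLE only are therefore possible.

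**4. The stated kappa.** The protocol gives 0.74. Take 71 of 78 recognised (Synopsis) and 120 patients: both positive 71, navigation only 7, pCLE only 7, neither 35.
- Observed agreement: (71 + 35) / 120 = 0.883
- Chance agreement: (78 × 78 + 42 × 42) / 120² = 0.545
- Kappa: (0.883 − 0.545) / (1 − 0.545) = 0.744

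Using 70 of 78 (opening summary), the table 70/8/6/36 gives 0.746. Reproducing a value near 0.74 in 120 patients thus takes 6 or 7 pCLE-only patients. By step 3, these can arise only through repositioning of the navigation device.

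**5. What the extra attempts are worth.** The protocol gives no per-attempt success rate, so this is an illustration. Assume independent placements with success probability p, all three used if needed. The chance of at least one success is 1 − (1 − p)³.

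| p (one attempt) | three attempts |
|---|---|
| 0.40 | 0.784 |
| 0.50 | 0.875 |
| 0.65 | 0.957 |

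Independence, and use of all three attempts, probably overstate the gain. The point is its source: more navigation attempts on one side of the comparison than on the other.

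**The case against.** **The comparison is not empty.** Because III.3.1 scores navigation on the first attempt and pCLE on any attempt, the two results can differ in both directions, and the protocol says so. This stands. What it does not do is turn the extra cases into localisation by pCLE: each later position is still reached with EBUS or EMN. At most they show that pCLE feedback helps to correct the position, which is the aim in III.2.1.

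**The protocol already states the narrower aim.** III.2.1 and III.3.1 come close to the right wording, and the Synopsis discloses that both techniques share a catheter. This also stands, and it makes the remedy easy. It leaves objective 1 and hypothesis (a) claiming something else.

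**A stronger reading is tempting.** A reader might infer that all 120 − 78 = 42 navigation-negative patients are negative on both techniques by construction, so that the all-patient kappa is inflated by a known amount. The documents do not support this. Step 3 shows how such a patient can become pCLE-positive. Entry to confocal imaging depends on localisation, whereas navigation-positive depends on a conclusive biopsy, so some of the 42 may well be imaged. If the pCLE-only cell were empty, 71 of 78 recognised would give a kappa of 0.88, not the stated 0.74. Nor is a kappa of 0 within the 78 informative: it is 0 whatever pCLE shows, because everyone there is navigation-positive.

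**Conclusion.** The concern holds against objective 1 and hypothesis (a), and against any conclusion drawn in their terms. It does not hold against III.2.1, which this design can address. The data remain usable; the claim of non-inferior or equally sensitive localisation is unsupported whatever the results, because no patient has a described path in which pCLE localises without navigation.

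No numerical bias is attached to this. The finding rests on II.1.1 and IV.4 being followed as written. The one-against-three asymmetry rests on the scoring in III.3.1; the positivity definition for navigation in section I does not mention a first attempt. Since the objective, the order of procedures and the positivity rules are all fixed in the protocol, an analysis plan could not supply the missing independent pCLE result.

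**What to change.** 1. Reword objective 1, hypothesis (a) and the planned conclusion to match III.2.1 and III.3.1: the proportion of nodules localised and sampled by navigation in which pCLE shows a solid pattern, reported with a confidence interval against the stated 90% criterion.
2. Report patients who are pCLE-positive but navigation-negative at the first attempt separately, as an adjunct (repositioning) effect, not as evidence of non-inferiority or superiority for localisation.
3. Do not use the all-patient kappa as support for non-inferior localisation.
4. Reconcile the Synopsis, where all 120 are explored by both techniques, with II.1.1, where the nodule is imaged after successful navigation.

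The cost is a narrower claim; procedures and recruitment need not change. The change should stop at the objective and the conclusion. Replacing the paired test in III.3.2 by a formal test against 90% would be more than rewording. With 78 patients and an exact one-sided 5% test, success needs 75 of 78: P(X ≥ 75 | 0.90) = 0.041, whereas P(X ≥ 74 | 0.90) = 0.099. Power would be about 45% if true recognition is 95%, and about 79% if it is 97%. If that route is taken, the threshold and power must be restated.

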**Main assessment criteria:**

1. number of lesions localized by confocal endoscopy compared to navigational bronchoscopy
2. Positive and negative predictive values of confocal signs before and after IV fluorophore injection for the diagnosis of cancer.

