### *III.3.3. Secondary criteria analysis :*

Positive predictive value of confocal imaging for the differentiation of benign versus malignant lesion will be calculated based on histology of the lesion and pertinent in vivo imaging items that will be describe during the study. This semiology will be described from the first 30 patients (including 20 malignant lesions) among the 78 patients for which a definite diagnosis is obtained by the procedure.

The value of this semiology will be confirmed on the 48 further patients.

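### Images after fluorescein are promised without condition, but the injection is given only after a solid pattern, so post-injection predictive values exist only for a selected, nested subset of the 78

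*Protocol*

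**What the plan says.** **What is promised.** The Synopsis, under Experimental plan, states: "120 subjects with peripheral lung nodule requiring navigational bronchoscopy will be included in the study and explored using both Confocal endoscopy AND navigational bronchoscopy". It goes on to say that "confocal images will be recorded before and after fluorescein IV injection, and before sampling". The Experimental plan in the opening summary carries the same imaging statement. Neither makes the injection depend on a finding.

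**What it is for.** The second main assessment criterion is "Positive and negative predictive values of confocal signs before and after IV fluorophore injection for the diagnosis of cancer". The opening Experimental plan and the Synopsis's Statistical evaluation say that signs of cancer will be assessed in the first 30 patients, using images from before and after injection, and confirmed in the following 48. III.3.3 draws the first 30 from "among the 78 patients for which a definite diagnosis is obtained by the procedure", so 30 + 48 uses up all 78.

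**What is done.** II.1.1 starts from a reached nodule: "After a successful tentative of nodule localisation using navigational bronchoscopy, the cellvizio miniprobe will be introduced into the extended working channel". Then: "When a solid confocal pattern is obtained, an IV injection of 5 ml fluoresceine sodium 1% will be performed", so that a further image can be taken ahead of the biopsy. For the others: "A maximum of three attempts to obtain a solid pattern using confocal will be authorized in each patient, after what the procedure will be considered" failed. No injection is described for them.

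**Two linked definitions.** III.3.1 calls alveoscopy negative when the pattern is normal and the biopsy at the same place is conclusive, so a confocal-negative nodule can have a diagnosis. II.1.3 lists the solid pattern among the items coded as possible discriminators of benign from malignant lesions, beside the vascular pattern after fluorescein.

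**The concern.** The imaging promised in the two Experimental plan sections and the injection rule in II.1.1 cannot both hold unless every nodule shows a solid pattern. The protocol does not expect that, since its success threshold is below 100%.

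Two things are at stake. First, the stated sets of 30 and 48 are not fully available for any sign read after fluorescein. Second, the pre-injection confocal result decides who has a post-injection image, and that result is itself one of the coded candidate signs. Within the injected patients the solid pattern does not vary, and post-injection PPV and NPV say nothing about nodules without it. The protocol does not say whether the pre-injection values use all diagnosed nodules or only the solid ones. If the two sets of values were reported on different denominators, they could differ although the sign behaved identically.

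**Working it through.** **1. The protocol's own numbers.** III.3.2 gives 78 navigation-positive patients and a forecast sensitivity of 65%: 78 / 0.65 = 120, which reproduces the stated total. The cancer-sign sets add up to 30 + 48 = 78.

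**2. How many have post-injection images.** Under II.1.1 the number is 78 × s, where s is the share of the diagnosed nodules that show a solid pattern. The protocol gives no forecast of s, only a success threshold: 70 of 78 (opening Experimental plan), 71 of 78 (Synopsis) or 90% (III.3.1; 0.90 × 78 = 70.2). I treat a nodule not recognised by confocal as one without a solid pattern.

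- At 71: 78 − 71 = 7 without images, 7/78 = 9.0%.
- At 70: 78 − 70 = 8 without images, 8/78 = 10.3%.
- Assumed range of s:
  - 100%: 78 with, 0 without
  - 95%: 74.1 with, 3.9 without
  - 80%: 62.4 with, 15.6 without
  - 70%: 54.6 with, 23.4 without

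Against the 120 subjects for whom the Synopsis announces the imaging, the 90% case gives 70.2/120 = 58.5%.

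**3. What a change of denominator could do.** Assumptions, none of them forecasts in the protocol:

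- The 20-in-30 malignant share of III.3.3 extends to all 78: 52 malignant, 26 benign.
- The sign has sensitivity 0.80 and specificity 0.80, identical before and after injection.
- Eight nodules have no post-injection image, and within the malignant and within the benign nodules the loss is unrelated to the sign.

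With M malignant and B benign nodules in the set:

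PPV = 0.80·M / (0.80·M + 0.20·B); NPV = 0.80·B / (0.80·B + 0.20·M)

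| Set | M | B | PPV | NPV |
|---|---|---|---|---|
| All 78 | 52 | 26 | 41.6/46.8 = 0.889 | 20.8/31.2 = 0.667 |
| 8 missing, all benign | 52 | 18 | 41.6/45.2 = 0.920 | 14.4/24.8 = 0.581 |
| 8 missing, 4 of each | 48 | 22 | 38.4/42.8 = 0.897 | 17.6/27.2 = 0.647 |
| 8 missing, all malignant | 44 | 26 | 35.2/40.4 = 0.871 | 20.8/29.6 = 0.703 |

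NPV moves by between −8.6 and +3.6 points although the sign has not changed.

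**4. When NPV does not move.** Among all 78 there are 20.8 true negatives and 10.4 false negatives, a ratio of 2 to 1. Suppose the 8 missing are sign-negatives lost in that ratio (5.33 and 2.67). NPV is then (20.8 − 5.33) / (31.2 − 8) = 15.47/23.2 = 0.667, as before.

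**5. Same-patient comparison.** Every injected nodule was imaged before its injection. Restricting both sets of values to the injected nodules gives them the same M and B, and an unchanged sign then shows no difference.

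**The case against.** Several points on the other side stand and limit the finding.

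- **The criterion does not ask for all patients.** A reader might infer that the second main criterion requires both images in everyone. Its wording sets no population. The unconditional imaging comes from the Experimental plan sections, and III.3.3, which does not mention fluorescein, limits the sign work to diagnosed patients.
- **The sets are nested.** A reader might infer that values before and after injection must come from different patients. They need not, because every injected patient also has a pre-injection image. A mismatch is a risk left open, not a consequence of the design.
- **Non-solid does not mean called benign.** It is tempting to say that the injection rule removes just the patients whom confocal would call cancer-free. The protocol uses the solid pattern chiefly to show that the lesion has been reached, whether benign or malignant, and gives no direction for its link with cancer. Judging malignancy only where lesion tissue is seen can be defended. What remains is that II.1.3 also codes the solid pattern as a candidate discriminator, so selection on a sign is possible.
- **Large swings need extreme losses.** With 85% sensitivity and 75% specificity, NPV on all 78 is 19.5/27.3 = 71%. Removing 7 true negatives gives 12.5/20.3 = 62%; removing 7 of the 7.8 false negatives gives 19.5/20.3 = 96%. Nothing in the protocol suggests either pattern. A loss of 5 true and 2 false negatives gives 14.5/20.3 = 71%, no change.
- **Precision is low in any case.** In the 80%/80% illustration, NPV rests on about 31 sign-negatives, with a 95% half-width of 1.96 × √(0.667 × 0.333 / 31.2) = 0.165. The possible shift is smaller than that, though it would be systematic.
- **Analysis sets are commonly left to the SAP, and no objective is to measure the gain from fluorescein.** Both are fair. But who is injected is a procedural rule that an SAP cannot settle, and the 30 + 48 are figures in the protocol that conflict with that rule.

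**Conclusion.** The inconsistency is real and moderate in size. The protocol announces images before and after fluorescein without condition and builds 30 + 48 = 78 patients on them, explicitly for the 30 and by implication for the 48. II.1.1 delivers the post-injection image only to nodules with a solid pattern. At the protocol's own threshold about 7 to 8 of 78 (9 to 10%) would lack it; the gap is larger if fewer nodules are solid and vanishes only if all are.

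Post-injection PPV and NPV are therefore conditional on a solid pattern. If the pre-injection values were taken on all 78, NPV could shift by several points from the change of denominator alone: 0.667 to 0.58 or 0.70 under the assumptions shown, with no shift under proportional loss. The protocol does not say that the values will be computed this way; it leaves the set undefined.

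A reader might infer that the main conclusion of the trial is at risk. It is not: the primary localisation criterion and the 78 and 120 do not depend on the injection.

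**What to change.** Reconcile the two Experimental plan sections and the Synopsis's Statistical evaluation with II.1.1 on who receives the injection. Which rule applies is for the sponsor to settle.

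If the conditional rule stands:

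1. Compute the before and after values in the same patients, those with both recordings of the same nodule.
2. Label the post-injection PPV and NPV as conditional on a solid pattern.
3. Restate the 30 + 48, for signs read after fluorescein, as the injected patients.

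The cost is wording and one analysis restricted to paired recordings, with no extra patients or procedures. The downside is a slightly smaller stated number for the fluorescein signs: about 70 or 71 rather than 78 at the protocol's threshold.
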